### Participants and Recruitment

#### Inclusion Criteria

Participants must be living with probable subthreshold depressive disorder (scoring 5-9 on the PHQ-8); be currently living with one or more long-term physical health conditions; be aged ≥18 years; have access to the internet (via phone, desktop, or laptop at any location, including at home, at the workplace, or free Wi-Fi in public spaces); have sufficient English proficiency to engage with the platform (self-assessed during screening); and have the ability to provide informed consent (ie, no known circumstances or conditions that may affect the capacity to consent).

Although there are no restrictions on the type of long-term condition (refer to Multimedia Appendix 1 for a list of common long-term condition options presented to interested participants), the long-term condition must be a diagnosed physical medical condition with a duration of ≥6 months that demonstrates recurrence or deterioration and is typically associated with a poor prognosis [34].

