#### Participant Timeline and Study Procedures

The flow of participants through the trial is summarized as follows (and illustrated in Figure 1): (1) recruitment (T_1_); (2) consent to take part in eligibility screenings (T_1_); (3) first eligibility screening (T_1_); (4) wait period; (5) second eligibility screening, consent to trial, and baseline assessment (T_2_); (6) randomization (T_3_); (7) intervention period (T_4_); (8) midintervention assessment (T_5_); and (9) follow-up assessment and qualitative interviews (T_6_).

All interested individuals will be directed to the trial URL or QR code on the recruitment materials to access the online participant information sheet hosted on Qualtrics (Qualtrics International Inc; T_1_). Participants will have the opportunity to contact the research team with any questions. Those who read the study information and decline to consent will be asked to anonymously indicate their reasons for declining to identify potential recruitment barriers. Those interested will consent to the eligibility screenings and complete the first screening (T_1_). Participants who are living outside the United Kingdom, are aged ≤17 years, do not have access to the internet, do not have a long-term physical health condition, do not have sufficient English proficiency, do not have the capacity to consent, or are living with a diagnosis of dementia or a severe mental health condition (bipolar disorder, psychosis, PTSD, or schizophrenia) will be informed that they are not eligible for the trial. All ineligible participants will be provided with information on available support and invited to contact the research team for further information.

Participants meeting all the inclusion criteria will be invited to enter the wait period. Participants ineligible at T_1_

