*based solely on their PHQ-8 score* will also be invited to enter the wait period as PHQ-8 scores and, therefore, eligibility may change over time. The wait period is necessary so that all participants randomized to the peer support platform gain access simultaneously, maximizing the opportunity for discussion and the formation of a community. The wait period is a trial design feature and would not be necessary if CommonGround were implemented in the health care system as people with long-term health conditions could immediately enroll and gain access to the preexisting community. During the wait period, participants can opt in to receive recruitment updates via email and can access a live URL summarizing recruitment progress via the study website. The wait period will finish when the recruitment target is met (N=150). Participants will then be invited to complete the second, shorter screening via individually generated Qualtrics links to assess their eligibility on two time-varying inclusion and exclusion criteria (T_2_): (1) meeting the criteria for probable subthreshold depressive disorder (scoring 5-9 on the PHQ-8) and (2) no new diagnosis received during the wait period of bipolar disorder, psychosis, PTSD, schizophrenia, or dementia.

All individuals found to be eligible at the second screening will be invited to consent to the fRCT and complete the baseline assessment (T_2_). Participants have 2 weeks to complete consent and baseline assessments via their individually generated Qualtrics link. The research team will contact participants who do not respond to the rescreening invitation a maximum of 3 times via email, with a follow-up phone call if necessary. Those individuals who are found ineligible for the fRCT solely due to their PHQ-8 score (ie, they satisfy all other inclusion criteria) and have PHQ-8 scores of ≤4 or within the range of 10 to 14 will be offered the opportunity to consent to a community engagement observational cohort. Participants in the community engagement observational cohort will be onboarded onto CommonGround alongside trial participants and engage with the platform as they wish during the 3-month intervention period. The community engagement cohort will increase the size of the peer community, potentially facilitating the intervention to gain traction. The protocol for the engagement cohort is available in Multimedia Appendix 2 and is not described further in this paper.

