#### Clinical and Health Economic Outcomes

Clinical outcomes will be measured for all participants at baseline (T_2_) or the postintervention time point after the 3-month intervention period (T_6_). All clinical outcomes will be treated as exploratory as this feasibility trial is not powered to evaluate clinical efficacy. These outcomes are (1) incidence of probable major depressive disorder at the postintervention time point only (T_6_), measured using the PHQ-8 [30] (PHQ-8>9=1; PHQ-8≤9=0); (2) symptoms of depression at the midintervention (week 6; T_5_) and postintervention (T_6_) time points, measured using the PHQ-8 total score [30]; (3) well-being at the postintervention time point (T_6_), measured using the Warwick-Edinburgh Mental Well-Being Scale [31]; (4) symptoms of anxiety at the postintervention time point (T_6_), measured using the Generalized Anxiety Disorder scale total score [45]; (5) health-related quality of life at the postintervention time point (T_6_), measured using the 36-Item Short Form Health Survey [46]; (6) social connectedness at the postintervention time point (T_6_), measured using the Social Connectedness Scale–Revised [47]; (7) self-efficacy in managing their health at the postintervention time point (T_6_), measured using the Chronic Disease Self-Efficacy Scales [48]; and (8) sense of virtual community at the postintervention time point (T_6_), measured using the sense of virtual community questionnaire [49] and an adapted 3-item entitativity measure [50,51].

The following measures will be used for the health economic outcomes:

The EQ‐5D‐5L, a standardized measure of health status consisting of 5 dimensions [52]. Standard value sets are summarized using a single index value determining the valuation of health-related quality of life [53].The Client Service Receipt Inventory [54]. We will use an adapted version of the Client Service Receipt Inventory that measures services and supports that a participant may have used over the previous 3 months. Subsections include accommodation and living situation, employment history, health care service use, and informal support.

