### Statistical Analysis

We will follow the CONSORT (Consolidated Standards of Reporting Trials) 2010 statement extension for randomized feasibility and pilot trials [57] For this protocol, we have followed the SPIRIT (Standard Protocol Items: Recommendations for Interventional Trials) checklist (Multimedia Appendix 5). We will describe feasibility outcomes, use metrics, and clinical outcomes using appropriate summary statistics (eg, mean and SD, median and IQR for normally distributed continuous outcomes, and counts and proportions for categorical outcomes). As the clinical outcomes have been selected for their relevance for informing potential effect sizes for a future confirmatory trial, regression models will be used to estimate the effect of treatment allocation on outcomes measured at the postintervention time point (T_6_). The analysis of clinical outcomes will follow a modified intention-to-treat principle. All eligible, randomized participants with a recorded outcome (ie, the outcome is not missing) will be included in the analysis and analyzed according to the treatment to which they were randomized. For binary outcomes (incidence of probable major depressive disorder at the postintervention time point), we will conduct a binary logistic regression where the model includes terms for treatment allocation (peer support platform=1; control arm=0), the baseline severity minimization factor (high=1; low=0), and the baseline value of the outcome. If the binary outcome of major depressive disorder is common (eg, >20%), we will consider robust Poisson models instead, following the work by Zou [58]. For linear outcomes (eg, symptoms of depression at the postintervention time point), we will use linear regression with the same covariates. Exploratory treatment effects will be estimated based on the coefficients for treatment allocation; 95% CIs will be estimated using bootstrapping. Given the sample size and purpose of this feasibility trial, all estimates of treatment efficacy will be treated as underpowered and not used as the basis for inferential statements. To inform sample size estimation for a future confirmatory trial, we will calculate the SD of the continuous clinical outcomes.

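### The logistic model for probable major depressive disorder includes a baseline covariate that is 0 for every eligible participant, so the term cannot be estimated and adds nothing to the two-level severity factor

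*Protocol article*

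**What the plan says.** The Statistical Analysis section names one binary clinical outcome, probable major depressive disorder after the intervention. Its logistic model contains treatment allocation, "the baseline severity minimization factor (high=1; low=0), and the baseline value of the outcome". If the outcome is common (the example given is above 20%), robust Poisson models will be considered instead, and no separate covariate list is given for them. For the continuous outcomes, "we will use linear regression with the same covariates". Confidence intervals come from bootstrapping.

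Four other statements bear on the covariate:

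- **Outcome coding** (Clinical and Health Economic Outcomes): the outcome is "incidence of probable major depressive disorder at the postintervention time point only (T_6", coded "PHQ-8>9=1; PHQ-8≤9=0".
- **Entry range** (Inclusion Criteria): "Participants must be living with probable subthreshold depressive disorder (scoring 5-9 on the PHQ-8". The Participant Timeline and Study Procedures section repeats the requirement at the second screening: "meeting the criteria for probable subthreshold depressive disorder (scoring 5-9 on the PHQ-8". That section lists the step as "second eligibility screening, consent to trial, and baseline assessment (T_2", so screening and baseline share a time point, and Table 1 shows one PHQ-8 entry there.
- **Analysis set** (Statistical Analysis): "All eligible, randomized participants with a recorded outcome (ie, the outcome is not missing) will be included in the analysis".
- **Minimization factor** (Randomization): low is a PHQ-8 score below 7, high is 7 or more.

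**The concern.** The model adjusts a threshold outcome for its own baseline value in a trial that admits only people below the threshold. The covariate is then a constant. A constant cannot be separated from the intercept, so the model as written has one more parameter than the data can identify.

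What is at stake is limited. The analyst cannot fit the model literally and must choose between dropping the term and substituting the PHQ-8 score. The two choices condition on different information and so give somewhat different adjusted odds ratios. The trial statistician is unblinded and data collection is complete, so the choice should be recorded openly. The third objective of the trial is to supply parameters for a confirmatory trial, and it names preliminary treatment effects among them, so it should be clear which model produced the reported estimate.

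**Working it through.** The protocol gives no figure of its own on this point, so the check starts from its definitions.

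**Step 1. Value of the covariate.** Apply the outcome coding (1 if above 9) and the minimization cut (1 if 7 or more) to every eligible baseline score:

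| T2 PHQ-8 | Baseline value of the outcome | Minimization factor |
|---|---|---|
| 5 | 0 | 0 |
| 6 | 0 | 0 |
| 7 | 0 | 1 |
| 8 | 0 | 1 |
| 9 | 0 | 1 |

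The second column is constant, and the third varies. Participants outside 5 to 9 are not eligible and so not in the analysis set.

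**Step 2. Rank of the model.** The design matrix has four columns: intercept, treatment, minimization factor, baseline outcome. The last is all zeros. The rank is 3 of 4 at N = 150 (target), 125 (number randomized) and 120 (80% of 150). Every bootstrap resample inherits the same constant column.

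**Step 3. What software does.** In one simulated data set (N = 120, 2:1), a standard logistic fit of the four-column model stopped with a singular-matrix error. A fit using a pseudo-inverse set the fourth coefficient to 0 and gave a treatment coefficient of -1.220 (SE 0.543), identical to the model without the term.

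**Step 4. The replacement covariate.** With the continuous T2 PHQ-8 score in the fourth column, the rank is 4 of 4. Its overlap with the minimization factor, assuming scores spread evenly over 5 to 9, is:

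- variance of the score = (4 + 1 + 0 + 1 + 4)/5 = 2
- variance of the factor = 0.6 × 0.4 = 0.24
- covariance = (7 + 8 + 9)/5 − 7 × 0.6 = 4.8 − 4.2 = 0.6
- correlation = 0.6/√(2 × 0.24) = 0.866, squared 0.75
- variance inflation factor between the two = 1/(1 − 0.75) = 4.0

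This overlap concerns the two baseline terms, not treatment.

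**Step 5. Effect on the treatment term.** Simulations used N = 120, 1,000 runs per setting, scores spread evenly, and assumed log-odds slopes per PHQ-8 point. Median SE of the treatment coefficient:

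| Assumed slope | Factor only | Score only | Factor and score |
|---|---|---|---|
| 0.2 | 0.542 | 0.543 | 0.549 |
| 0.35 | 0.531 | 0.534 | 0.540 |
| 0.6 | 0.522 | 0.535 | 0.539 |

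The largest difference between factor only and both terms is 0.539 − 0.522 = 0.017. In that setting the median coefficient also moved, from -0.572 to -0.606, as adjustment in a logistic model tends to do. The SE column should therefore not be read alone as a gain or loss.

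**The case against.** The best case for the plan has four parts.

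**A workable meaning can be supplied.** The binary outcome is defined only at T6, so the baseline value might be taken as the T2 PHQ-8 score, the only related measurement available. The phrase also works for the linear models, which share the covariate list. But the section on clinical outcomes lists incidence and the PHQ-8 total score as separate outcomes. The phrase stands in the sentence written for the binary outcome, and nothing redefines it. If the score was meant, the text still has to say so. An analysis plan that is not shown may do this, but the article states a covariate set that fails by its own definitions, which differs from leaving detail out.

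**The practical consequence is small.** This stands. Dropping the column returns the three-term estimate unchanged. A reader might infer that the treatment effect is biased or that the analysis cannot be done. Step 3 shows otherwise.

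**Baseline severity is still adjusted for.** This also stands. A reader might infer that baseline adjustment is lost altogether, but the minimization factor stays and only differences within its two levels go unused (5 versus 6; 7, 8 and 9). The part of the score that the factor does not explain (1 − 0.75 = 25% under the even-spread assumption) is variance of a covariate, not of the outcome, and does not measure harm to the result. Nor does the document show how strongly the baseline score predicts crossing the threshold.

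**The outcome is exploratory.** The primary outcome is recruitment, the progression criteria in Table 2 do not use clinical outcomes, and efficacy estimates are not to support inferential statements. The incidence itself can be reported from counts and proportions without this model. This limits the weight of the point but does not remove the error.

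**Conclusion.** The error is certain on the document's definitions: the covariate is 0 for every analysed participant, it is collinear with the intercept, and its coefficient cannot be estimated. The one thing taken as read is that the T2 PHQ-8 serves both the second screening and the baseline, as Table 1 shows and as the adverse event section implies by describing baseline scores as 5 to 9.

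The size is small. The written adjustment contributes nothing beyond the minimization factor, and the treatment estimate is neither biased nor changed from the model without the term. The linear model for depressive symptoms is unaffected, because its baseline score varies. The 0.87 correlation and the simulated standard errors rest on an assumed even spread of scores and assumed slopes. They show no precision gain from the replacement, and none is claimed. This is a minor specification correction to an exploratory analysis and does not threaten the trial's feasibility conclusions.

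**What to change.** For probable major depressive disorder, replace the baseline value of the outcome with the continuous T2 PHQ-8 total score, alongside treatment and the minimization factor, and state that the robust Poisson alternative uses the same terms. This matches the pair of baseline terms that the linear model for PHQ-8 symptoms already carries. Keep the baseline value of the outcome for the continuous outcomes measured at baseline.

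Deleting the term and stating that only the minimization factor is used would also make the model estimable, but would leave out the adjustment within severity levels that the extra term was evidently meant to supply.

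The cost is one sentence in the analysis section or the analysis plan, with no new data. As data collection has ended, date the change and give the reason for it.

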#### Sample Size

Sample sizes ranging between 24 and 50 are commonly recommended for feasibility studies, with Teare et al [37] recommending 70 participants for a 2-arm RCT (35 per arm). However, larger samples are typically required for online, group-based peer support interventions to gain traction as this form of peer support depends upon interactions among a large number of participants to maximize the volume of discussions and interactions that develop a sense of community. Therefore, to ensure an adequate group size for the platform, we aim to recruit 150 participants and randomize them 2:1 into intervention and control arms, respectively. Recruitment is expected to last 10 weeks. Recruiting 150 participants will allow us to estimate an expected recruitment rate (primary feasibility outcome: number recruited to the trial per week) of 15 participants per week (95% CI 12.7-17.6) based on an exact Poisson test. Given the aims of this feasibility trial, no power calculations for clinical outcomes were conducted.

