### Randomization

#### Overview

Participants will be individually randomized (T_3_) using the King’s Clinical Trials Unit web-based randomization service upon completion of their baseline questionnaires (T_2_) by a research assistant. Online peer support requires a sufficiently large community of active users to enable discussions and foster a community. Therefore, we will allocate participants using a 2:1 ratio (100 to the intervention arm and 50 to the control arm). Treatment allocations will be stratified based on baseline depressive symptom severity using minimization with randomly varying block sizes. Baseline depressive symptom severity will be measured using the PHQ-8 total score (low=PHQ-8 score of <7; high=PHQ-8 score of ≥7). Although the research team will be unblinded to treatment allocations, the web-based system will conceal subsequent allocations.

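### The T6 PHQ-8 linear model leaves out the T1 screening PHQ-8, so the exploratory treatment effect probably loses a little precision

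*Protocol article*

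**What the plan says.** All references are to the protocol article.

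- **Statistical Analysis.** Beside treatment allocation, the binary model contains "the baseline severity minimization factor (high=1; low=0), and the baseline value of the outcome". For continuous outcomes, "we will use linear regression with the same covariates".
- **Randomization (Overview).** The minimization factor is the T2 PHQ-8 in two classes: "low=PHQ-8 score of <7; high=PHQ-8 score of ≥7".
- **Participant Timeline and Study Procedures.** The second screening at T2 requires a PHQ-8 score of 5 to 9. The first screening at T1 comes before it for everyone. People who fail at T1 on the PHQ-8 alone "will also be invited to enter the wait period as PHQ-8 scores and, therefore, eligibility may change over time".
- **Table 1.** PHQ-8 is ticked at T1, T2, T5 and closeout (T6).
- **Objectives; Clinical and Health Economic Outcomes; Statistical Analysis.** Preliminary treatment effects are a stated objective. The clinical outcomes are exploratory, and their effect estimates are not to support inferential statements.

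No section uses the T1 PHQ-8 as a covariate.

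**The concern.** Baseline adjustment narrows an interval to the extent that the baseline predicts the outcome. Selecting on a narrow band of the baseline removes much of that predictive value. In this trial the T2 PHQ-8 can take only five values among those randomized, and the second covariate is a coarsening of the same reading. The PHQ-8 model therefore carries little prognostic information.

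A second pre-randomization reading of the same scale has already been collected and is not restricted to that band. T1 and T2 are both noisy readings of underlying severity, so T1 may still say something about T6 once T2 is known. What is at stake is the width of the interval around the exploratory PHQ-8 effect, which is one of the inputs meant to inform a confirmatory trial.

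**Working it through.** **1. The plan's own figure.** The Sample Size section gives only one computed figure: "15 participants per week (95% CI 12.7-17.6) based on an exact Poisson test". With 150 events in 10 weeks, the exact limits are χ²(0.025; 300)/2/10 = 12.70 and χ²(0.975; 302)/2/10 = 17.60. The figure reproduces. It says nothing about the clinical models, for which "no power calculations for clinical outcomes were conducted". The size of the present point therefore rests on assumptions.

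**2. How much T2 can explain.** Five equally likely integers from 5 to 9 have variance (25 − 1)/12 = 2, so SD ≈ 1.4. Simulated PHQ-8 scores were rounded to 0-24 and selected to 5-9 at T2. The assumed screening means were 7 to 10, SDs 4 to 5.5 and equal correlations 0.4 to 0.8. The results were:

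- T2 SD about 1.4, against a T1 SD of about 2.7 to 4.9 among those selected;
- planned terms (factor plus T2) explaining about 1% to 17% of T6 variance.

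By hand, at an assumed SD of 5 and r = 0.7: the explained part is 0.49 × 1.4² ≈ 0.96, the residual is 25 × (1 − 0.49) = 12.75, and R² ≈ 0.96/13.71 ≈ 7%. The simulation with mean 8 also gives 7%.

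**3. What T1 would add.** The proportional cut in residual variance is the squared partial correlation of T1 and T6 given T2:

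ρ = (r₁₆ − r₁₂r₂₆) / √[(1 − r₁₂²)(1 − r₂₆²)]

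Under joint normality, selection on T2 leaves this unchanged. With all three correlations equal to r it becomes r/(1 + r). The standard error falls by 1 − √(1 − ρ²).

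| Assumed correlations | Cut in residual variance | Cut in SE |
|---|---|---|
| Equal, r = 0.5 | (0.5/1.5)² = 11% | 6% |
| Equal, r = 0.6 | (0.6/1.6)² = 14% | 7% |
| Equal, r = 0.7 | (0.7/1.7)² = 17% | 9% |
| r₁₂ = r₂₆ = 0.7, r₁₆ = 0.6 | (0.11/0.51)² = 5% | 2% |
| First-order severity with error: reliability 0.80, adjacent true correlation 0.8 (r₁₂ = r₂₆ = 0.64, r₁₆ = 0.512) | (0.1024/0.5904)² = 3% | 2% |
| Pure first-order decay of the observed scores (r₁₂ = r₂₆ = 0.7, r₁₆ = 0.49) | 0% | 0% |

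The simulated cuts agree with the closed form in the equal, mixed and pure-decay cases. At an equal r of 0.4 the cut is 8%. An r of 0.8 would give 20%, but that is a strong assumption for readings separated by a wait and a 12-week intervention.

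**4. In PHQ-8 points.** At mean 8, SD 5 and equal r = 0.7, with 100 v 50 analysed, the 95% half-width goes from 1.19 to 1.09 and R² from 7% to 22%. With 80 v 40 (an assumed 80% response) it goes from 1.33 to 1.22. In the 0.7/0.7/0.6 case with 100 v 50 it goes from 1.19 to about 1.19 × √0.953 ≈ 1.16.

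**The case against.** The strongest reply is that nothing here is wrong. Adjusting for the minimization factor and the baseline value is standard, valid and unbiased, and further precision covariates are often left to a statistical analysis plan, which is not shown. The primary outcome is recruitment, no progression criterion in Table 2 uses a clinical effect, and the estimates are declared exploratory. All of this stands, and it makes the point optional.

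It is also fair that T1 may predict T6 less well than T2 does. T1 comes before T2 by a wait that differs between people: "Recruitment is expected to last 10 weeks", and the wait ends only when the target is met. That favours the lower rows of the table. A gain of exactly zero, however, needs first-order decay of the observed scores. If true severity is first-order but each reading carries error, T1 still adds something.

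A reader might infer more than the documents support:

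- **That every outcome model is affected.** Well-being, anxiety, quality of life, connectedness and self-efficacy each adjust for their own T2 score, which eligibility does not restrict. No gain has been shown for them.
- **That the interval for probable major depressive disorder would narrow.** In logistic regression, a prognostic covariate does not shrink the standard error of the log odds ratio. The calculation above covers the linear model only.
- **That the SDs for sizing a confirmatory trial are wrong.** The plan is to report outcome SDs, and covariate choice does not change those.
- **That 11-17% is worth 18 to 31 extra participants out of 150.** That takes the favourable correlations and complete follow-up. The Results section reports 125 randomized, and only those with a recorded outcome are analysed.
- **That T1 level is the main prognostic difference left between arms.** Nothing in the documents shows this.

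**Conclusion.** The point holds for one model, the T6 PHQ-8 linear regression, and is minor. Its only prognostic covariates are a T2 score restricted to five values and that score's own split, while an unrestricted pre-randomization reading of the same scale is left unused. Some precision is probably lost.

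The documents give no PHQ-8 mean, SD or correlation, so the size is an assumption throughout: residual variance lower by 0% to about 17% and standard error by 0% to about 9%, for equal correlations up to 0.7. A gain of a few percent is plausible. Even the favourable example is worth about a tenth of a PHQ-8 point in the half-width. The treatment estimate is not biased, and the feasibility conclusions do not change.

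**What to change.** In the Statistical Analysis section, add the continuous T1 PHQ-8 total as a covariate in the linear model for the T6 PHQ-8 score. Keep the T2 score and the minimization factor. Optionally, report the residual SD adjusted for T1 and T2 beside the planned outcome SD, so that a confirmatory trial that wishes to adjust for both can use it.

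The Results section states that data collection is complete. If analysis has already begun, report the T1-adjusted model as a labelled supplementary analysis and leave the planned model in place.

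The cost is one degree of freedom and one line in the analysis specification, with no new data, visits or participants.
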